### Statistical methods

We have developed a data management and statistical analysis protocol for the clinical trial. The protocol details the procedures for data entry, management, cleaning, and analysis. Two research assistants will enter the collected data into an Excel file, and they will compare the entered data to minimise data entry errors. The research assistants will also assess the intra-examiner agreement regarding caries diagnoses and the VPI at each time point using Cohen’s kappa statistics. The level of statistical significance for all two-sided tests will be set at 0.05.

We will perform the Cochran-Armitage test for trends in proportions with correction for clustering. In addition, we will explore the trend in the arrest rates of carious lesions with increasing SDF exposure (application) times, taking into consideration the effect of the moderating variables and the number of surfaces of the carious lesions. The power calculations will be based on a steady linear increase, and the power of the study will be less if a plateau is reached before 180 s. Thus, we will set the power at 90% in our sample size calculation and estimate the profile non-parametrically to see if any plateau is reached at a given time. EC80 (an 80% maximal concentration) analysis will be used to determine the exposure (the SDF application time) at which 80% of the carious lesions are arrested. Because individual children may have more than one lesion, we will use bootstrap methods for clustered data, and resample by cluster to determine the 95% confidence interval. An in-house statistician will perform statistical analyses using the software of IBM SPSS Statistics for Windows version 26 (IBM Corp. Armonk, NY, USA) and SAS OnDemand for Academics (SAS Institute, Inc., Cary, NC, USA).

This clinical trial will employ an intention-to-treat analysis to address dropouts. We will perform a sensitivity analysis (attributable estimand) to address the outcomes for those children not completing the 6-month study. We will assume that none of the treated teeth will be arrested among dropouts and thus will include dropouts in the sensitivity analysis. However, our experience from previous trials suggests that the number of children who will drop out in 6 months will likely be less than 1% [14, 18, 22].

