**Methods/design:**

The design is a stratified-randomised, double-blind, active-controlled, parallel-group clinical trial with nine treatment arms. The trial will involve recruiting at least 414 3- to 5-year-old kindergarten children with caries, who will receive approximately 0.004 mL of 38% SDF (the typical amount applied per the manufacturer’s instructions) to treat each caries lesion. The children will be stratified by caries status, randomised by blocks, and allocated to nine groups of SDF application times: 3, 5, 10, 15, 30, 45, 60, 120, and 180 s. The outcome measure is caries lesion activity (active/arrest) at the tooth-surface level at 6 months post-initial treatment. A calibrated dentist will conduct the blinded clinical examinations at baseline and at the 6-month follow-up. In addition, the parents will be surveyed to examine the effects of the moderating variables, such as oral hygiene, on caries lesion activity. The hypothesis is that a monotonically increasing trend can be found between the SDF application time and the proportion of caries lesions that are arrested. The Cochran-Armitage test for trends in proportions, corrected for clustering within children, will be used to determine the relationship between the exposure to SDF (the SDF application time) and the response (proportion of lesions arrested) in children, taking into consideration the effect of the moderating variables as well as the nesting of multiple caries lesions within an individual child. An EC 80 analysis (an 80% maximal concentration) will be used to determine the exposure (the SDF application time) for 80% caries lesion arrest. Bootstrap methods will be used for clustered data and will be resampled by clustering to determine the 95% confidence interval.

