### Randomisation and treatment allocation

The participating children with caries will first be categorised as either (1) having a high caries rate (or severe early childhood caries as defined by the American Academy of Paediatric Dentistry, 2008), which is defined as the presence of more than three untreated caries surfaces, or (2) having a low caries rate [16]. The children will be allocated via a stratified randomisation method with a block size of 18 into nine groups for the application of 38% SDF (Advantage Arrest Silver Diamine Fluoride 38%, Elevate Oral Care, FL, USA) on each carious lesion (Fig. 2):

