### Sample size and power calculation

The sample size is estimated based on a caries arrest rate of 70% [19] for a 60s application. We assume that a monotonically increasing trend exists and that the caries arrest rate is 80% for a 180 s application. Therefore, the expected caries arrest rates are 65.25%, 65.42%, 65.83%, 66.25%, 67.50%, 68.75%, 70.00%, 75.00%, and 80.00% for 3-s, 5-s, 10-s, 15-s, 30-s, 45-s, 60-s, 120-s, and 180-s applications, respectively. The power will be set at 90%, and the one-sided type I error (α) will be set at 0.025 (equivalent to a two-sided type I error of α = 0.05). The required sample size for detecting proportion trends is 104 surfaces of carious lesions per group [20]. In this study, the mean number of surfaces of carious lesions at baseline per child is estimated to be 4.75 [14]. In addition, the anticipated intraclass correlation coefficient is 0.23. This clinical trial requires 195 surfaces of carious lesions from 41 children per group following the equation for a multi-level study [21]. We assume that the dropout rate is 0.5% and the non-compliance rate is 10%. At least 46 children per group, or a total of 414 children at baseline, need to be recruited for this randomised clinical trial.

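### Randomisation is stratified by caries status, but the trend test named for the primary outcome leaves the stratum out, and the abstract and methods disagree on whether covariates enter it

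*Protocol article*

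**What the plan says.** **Randomisation.** Under Randomisation and treatment allocation, children are first classed as having a high caries rate, "which is defined as the presence of more than three untreated caries surfaces, or (2) having a low caries rate". Then: "The children will be allocated via a stratified randomisation method with a block size of 18 into nine groups". The abstract also says that children are stratified by caries status.

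**Primary test.** Under Statistical methods: "We will perform the Cochran-Armitage test for trends in proportions with correction for clustering". Clustering is the only correction named. The Discussion describes the test again, also without the stratum.

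**Covariates.** The abstract says that the Cochran-Armitage test will relate application time to arrest, "taking into consideration the effect of the moderating variables as well as the nesting of multiple caries lesions within an individual child". Statistical methods instead adds a second step in which the trend is to be explored, "taking into consideration the effect of the moderating variables and the number of surfaces of the carious lesions".

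**Sample size.** "The power will be set at 90%, and the one-sided type I error (α) will be set at 0.025". The assumed arrest rates run from 65.25% at 3 s to 80.00% at 180 s, and "The required sample size for detecting proportion trends is 104 surfaces of carious lesions per group". No arrest rate is given separately for the two strata.

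**The concern.** Blocking within strata makes caries status nearly equal across the nine arms. If caries status also predicts arrest, the part of the outcome variation that it explains can hardly contribute to a chance trend across arms. A test that ignores the stratum still counts that part in its variance. Its standard error is then too large, its two-sided type I error falls below 5%, and some power is given up. There is no risk of extra false positives from this source. The stake is efficiency: the protocol already warns that power will fall if arrest plateaus before 180 s, and the design has paid for the stratification.

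The second problem is one of description. The ordinary Cochran-Armitage test compares marginal proportions and has no covariate terms. The abstract implies a covariate-adjusted main analysis; the methods section describes an unadjusted test with an exploratory addition. These are different primary analyses. The choice matters because oral hygiene, visible plaque and the parental questionnaire are recorded at 6 months as well as at baseline, so the phrase about moderating variables could be read to admit values measured after treatment.

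**Working it through.** **1. Inputs from the protocol.** One-sided α 0.025, power 90%, nine application times, 4.75 surfaces per child, intraclass correlation (ICC) 0.23, dropout 0.5%, non-compliance 10%. The assumed arrest rates equal 0.65 + t/1200, with t in seconds.

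**2. Reproducing the plan's sample size with an unstratified trend test.** With seconds as the score x:

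- Mean score x̄ = 468/9 = 52; S = Σ(x − x̄)² = 29,348
- Mean rate p̄ = 0.6933; p̄(1 − p̄) = 0.21262
- A = Σp(x − x̄) = 29,348/1200 = 24.457
- √[p̄(1 − p̄)S] = √6240.0 = 78.99; √[Σp(1 − p)(x − x̄)²] = √5365.6 = 73.25
- n = [(1.960 × 78.99 + 1.2816 × 73.25)/24.457]² = 103.4, so 104 surfaces per group, as stated
- Design effect 1 + 3.75 × 0.23 = 1.8625; 104 × 1.8625 = 193.7 surfaces; 193.7/4.75 = 40.8, so 41 children; 41 × 4.75 = 194.75, so 195 surfaces
- 41/(0.995 × 0.90) = 45.8, so 46 per group; 46 × 9 = 414

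Every stated figure reproduces. The planned size therefore matches the planned unstratified test, scored in seconds.

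**3. Effect of leaving the stratum out.** The protocol gives neither the difference in arrest between strata nor the share of high-caries children. Both are assumed here: a difference of 0 to 30 percentage points (lower arrest in the high stratum) and a high-caries share of 40% to 60%. Each simulated trial had 41 children per arm, balanced within stratum. The low stratum had 1 to 3 surfaces, the high stratum 4 or more, with an overall mean of 4.75.

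Lesions were beta-binomial. The within-stratum ICC was reduced so that the total stayed near 0.23: 0.23 − d²f(1 − f)/(0.693 × 0.307), where d is the stratum difference and f the high-caries share. For d = 0.30 and f = 0.5 this gives 0.124.

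The cluster-robust Cochran-Armitage score test was run without strata and in its stratified (Mantel-extension) form, with 20,000 null and 8,000 power runs per scenario. Ranges are over the 40-60% share.

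| Stratum difference | Two-sided size, unstratified | Two-sided size, stratified | Power lost by leaving stratum out |
|---|---|---|---|
| 0 points | 0.050-0.053 | 0.050-0.054 | none |
| 10 points | 0.048-0.049 | 0.049-0.051 | within 0.2 point |
| 20 points | 0.043-0.048 | 0.047-0.053 | 0.5-0.8 point |
| 30 points | 0.037-0.041 | 0.050-0.052 | 1.2-2.5 points |

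At 30 points, power without and with the stratum was 83.8% and 86.3% (40% share), 86.5% and 88.6% (50%), and 88.7% and 89.9% (60%).

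**4. Two cautions on reading these results.** Absolute power in the simulation, about 80-90%, lies mostly below the planned 90% because unequal numbers of surfaces per child were assumed; that is a separate matter. The conservatism is also a two-sided statement. In the upper tail alone, against 0.025, the unstratified test rejected in 2.98-3.10% of null runs with no stratum difference and 2.45-2.59% at 30 points; the stratified test rejected in 2.72-2.86% at 30 points.

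**5. The two descriptions side by side.** The abstract has one analysis: the trend test, with moderators and nesting taken into account. Statistical methods has two: the trend test with a clustering correction, then an exploratory analysis with moderators and number of surfaces. No reading makes both the primary analysis.

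**The case against.** The strongest reply has five parts.

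- **The loss is conditional and small.** This stands. Without a stratum difference nothing is lost, and even at 30 points the loss is at most 2.5 points of power. A reader might infer that the planned test is certainly conservative and underpowered for this reason. The documents do not support that, because they give no arrest rates by stratum.
- **The sample size is consistent with the test.** This stands. All figures reproduce, and a single ICC of 0.23 used in an unstratified calculation is most naturally the total correlation, which already contains any between-stratum variance. That is why the total was held near 0.23 above.
- **The test can be stratified.** This also stands. A reader might infer that a Cochran-Armitage test cannot take the stratum, so the method must be abandoned. A Mantel-extension form exists; the test as named simply does not include the stratum.
- **The stratifying variable is already considered.** This stands in part. The additional analysis uses the number of carious surfaces, the variable on which the strata are cut. But it is exploratory and does not alter the primary test.
- **This is detail for the separate analysis protocol.** The article mentions such a document, which is not shown and may name the stratum. That would settle the test, but the abstract and the methods section would still disagree here. Analysing by the strata already used to randomise is also a better method than the one stated, at almost no cost.

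**Conclusion.** The point holds in a limited form. The named trend test omits the factor by which randomisation is stratified, and the abstract and Statistical methods describe different roles for the covariates. The statistical cost depends on an unknown: how far arrest differs between high- and low-caries children. Over an assumed 0 to 30 points it runs from nothing to about 2.5 points of power, always on the side of caution in the two-sided test. These figures also rest on the assumed surface counts, a 40-60% high-caries share and a total ICC near 0.23.

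This is an inexpensive improvement together with a contradiction to resolve. It does not make the planned test invalid, and it is no reason to enlarge the trial.

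**What to change.** - Make the primary test a cluster-corrected Cochran-Armitage trend test stratified by the randomisation stratum (Mantel-extension form), with application time in seconds as the score. This keeps the scoring on which the sample size rests. Keep the unstratified test as supportive.
- A child-clustered logistic model with time and stratum is an alternative, but it is not a neutral swap. It changes the effect scale from a trend in proportions to log-odds, and the working correlation can change how children are weighted against lesions. If it is preferred, those choices should be stated.
- Restrict any further covariates to baseline values, excluding 6-month plaque, oral hygiene and questionnaire answers.
- Reword the abstract so that it agrees with Statistical methods on which analysis is primary and where the moderating variables enter.

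The cost is wording in the protocol and the analysis plan, ideally settled before outcome data are seen. The simulation showed no measurable power penalty for stratifying when the strata do not differ, and the sample size need not change.

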This trial will use EC_80_ (80% maximal concentration) analysis. EC_80_ can be defined as the exposure (the SDF application time) required to obtain 80% of caries arrest. We will use the bootstrap method for clustered data, and perform resample by cluster to determine the 95% confidence interval. The bootstrap method uses simulation to calculate standard errors, confidence intervals, and significance tests, and it does not rely on many assumptions [28]. It resamples (with replacement) the sample data and creates a large number of phantom samples known as bootstrap samples. A major advantage of using the bootstrap method is its simplicity. It is a straightforward way of deriving estimates of standard errors and confidence intervals for complex estimators of the distribution. However, this method relies on a representative sample and can be time-consuming. This clinical trial will also employ an intention-to-treat analysis to address dropouts. Intention-to-treat analysis is a method for analysing the results of all children according to the groups to which they are assigned, regardless of what application times they received. This method generates an unbiased conclusion regarding the effectiveness of the intervention [29].

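### EC80 has a relative-to-maximum label but is used as the time to 80% arrest, which the planning rates put at 180 s, the edge of the tested range, so its upper confidence limit will seldom exist

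*Protocol article*

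**What the plan says.** Statistical methods: "EC80 (an 80% maximal concentration) analysis will be used to determine the exposure (the SDF application time) at which 80% of the carious lesions" have become arrested. The next sentence gives a bootstrap that resamples children for a 95% confidence interval, which I read as the interval for EC80.

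The abstract says the analysis "will be used to determine the exposure (the SDF application time) for 80% caries lesion arrest". The Discussion says EC80 "can be defined as the exposure (the SDF application time) required to obtain 80% of caries arrest". All three places attach the same percent-of-maximum label and then state an absolute target.

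Sample size and power calculation: "The sample size is estimated based on a caries arrest rate of 70% [19] for a 60s application", and it is assumed that "the caries arrest rate is 80% for a 180 s application". By arm, "the expected caries arrest rates are 65.25%, 65.42%, 65.83%, 66.25%, 67.50%, 68.75%, 70.00%, 75.00%, and 80.00" per cent. The abstract has children "allocated to nine groups of SDF application times: 3, 5, 10, 15, 30, 45, 60, 120, and 180 s", so 180 s is the longest time tested.

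Statistical methods also plans a non-parametric estimate of the arrest profile, to look for a plateau.

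**The concern.** There are two linked problems.

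First, the label and the use are different quantities. A percent-of-maximum EC80 depends on the fitted maximum, and perhaps on a baseline. The time to 80% arrest depends on neither. Someone programming from the label could compute a different number from someone programming from the sentence.

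Second, the absolute target equals the rate assumed for the last arm. An interval for a time at the edge of the tested range has nothing above it to close on: resamples in which the fitted curve stays below 80% have no solution within 180 s. If they were dropped, the interval would look finite when the data do not support an upper limit; if they were extrapolated, the limit would rest on times never studied. The article does not say that either will be done. But the trial is meant to help determine an application time, and EC80 is the time estimate to which it attaches a 95% interval.

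**Working it through.** **Inputs.** From Sample size and power calculation: the nine arrest rates; one-sided α 0.025; power 90%; 104 surfaces per group; 4.75 surfaces per child; intraclass correlation 0.23; 41 children per group, 46 after inflation.

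**Planning curve.** The nine rates are p(t) = 65% + t/12, with t in seconds. For example, 65 + 3/12 = 65.25, 65 + 60/12 = 70 and 65 + 180/12 = 80.

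**Reproducing the plan's sample size.** Cochran-Armitage with scores in seconds:

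n = [1.96·√(p̄(1−p̄)Σ(t−t̄)²) + 1.2816·√(Σp(1−p)(t−t̄)²)]² / [Σp(t−t̄)]²

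- t̄ = 468/9 = 52; Σ(t−t̄)² = 29,348; p̄ = 0.6933; Σp(t−t̄) = 29,348/1200 = 24.46.
- n = (1.96×78.99 + 1.2816×73.25)² / 24.46² = 103.4, or 104.3 with continuity correction. The plan states 104.
- Design effect 1 + 3.75×0.23 = 1.8625; 104×1.8625 = 193.7 surfaces; 193.7/4.75 = 40.8, so 41 children; 41×4.75 = 194.75, stated as 195.
- 41/(0.995×0.90) = 45.8, so 46; 46×9 = 414.

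The plan's figures reproduce, so the linear-in-seconds curve is the right basis for the check.

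**Where EC80 falls on that curve**, inverting as t = 12×(p − 65):

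| Reading | Target rate | Time |
|---|---|---|
| 80% of lesions arrested (the stated use) | 80% | 12×15 = 180 s, the upper edge |
| 80% of the maximum rate | 0.8×80 = 64% | 12×(−1) = −12 s, below the range |
| 80% of the rise from time 0 | 65 + 0.8×15 = 77% | 12×12 = 144 s, inside |
| 80% of the rise from the 3-s arm | 65.25 + 0.8×14.75 = 77.05% | 144.6 s, inside |

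**Hand check of the upper limit (absolute reading).** Effective surfaces per arm are 194.75/1.8625 = 104.6, so the SE at 180 s is √(0.8×0.2/104.6) = 0.039. Read from that arm alone, an upper limit for EC80 exists only if the lower 95% limit of the 180-s rate is at least 80%: p − 1.96√(p(1−p)/104.6) ≥ 0.80 gives p of about 86.5%. If the true rate is 80%, that is (0.865 − 0.80)/0.039 ≈ 1.67 SE above expectation, which happens in about 5% of trials.

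**Simulation at the planning rates.** Assumptions not in the article: beta-binomial lesions, 1 + Poisson(3.75) lesions per child, and the fitted curves (isotonic with interpolation; weighted straight line). There were 1,500 trials for point estimates, 300 of them bootstrapped with 300 resamples of children.

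| Result | 41 per arm | 46 per arm |
|---|---|---|
| 80% not reached by 180 s, isotonic | 49% | 45% |
| EC80 above 180 s or no estimate, straight line | 51% | 50% |
| Resamples with no in-range EC80, isotonic | 45% | 43% |
| Upper 95% limit undefined, isotonic | 95% | 94% |
| Upper 95% limit above 180 s, straight line | 97% | 97% |
| Lower 95% limit in range, isotonic | 100% | 99% |

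Monte Carlo SE is about √(0.25/1500) = 1.3 points for the first two rows and √(0.95×0.05/300) = 1.3 points for the upper-limit rows. Other isotonic runs at 41 per arm gave 45–51% not reached and 94–95% with no upper limit. A logistic curve gave 52% above 180 s and 96% with the upper limit above 180 s.

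**The case against.** The strongest reply is that the stated use is the same in all three places, so the label is a loose gloss. It even speaks of concentration when the exposure is time, and no sentence directs a calculation from a fraction of the maximum. That stands, and it limits the first problem to a wording correction.

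A reader might infer that EC80 falls at or outside the range under both definitions, at opposite ends. The documents do not support that. It requires reading the label as 80% of the total arrest rate (64%); read as 80% of the rise, EC80 is about 144 s and inside the range.

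A reader might also infer that the whole interval fails. Only the upper limit does. The lower limit is nearly always estimable, and the point estimate is in range about half the time. A finding that EC80 exceeds some number of seconds is still usable.

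Nor is EC80 the only analysis that could yield a time: the non-parametric profile could identify a plateau.

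Finally, the 90% power is for the trend test, not for EC80, and the article mentions a separate analysis protocol that is not shown. A rule for out-of-range estimates may be there, so its absence from the article is not the point. What remains is that the article sets the target at the rate it assumes for its last arm while promising a 95% interval.

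**Conclusion.** The point holds for the absolute definition. On the plan's own rates the target time is 180 s, the last time tested. About half of trials would not reach 80%, and about 94–97% would have no upper 95% limit within 180 s. The label mismatch is real but secondary.

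The location of EC80 follows from the article's figures alone. The percentages also rest on the clustering and curve assumptions listed above, though they change little between isotonic, linear and logistic fits, and on the planning rates being true. If arrest passes 80% before 180 s, EC80 moves inside the range; read from the 180-s arm alone, the true rate there would have to be about 86.5% for an upper limit to exist in half of trials. If arrest plateaus below 80%, a possibility given that the plan itself allows for a plateau, EC80 does not exist.

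This should be fixed, but it does not threaten the primary trend test.

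**What to change.** 1. Keep one definition, the application time at which 80% of lesions are arrested, and delete the percent-of-maximum label in the abstract, Statistical methods and Discussion.
2. Keep estimates and bootstrap resamples that fall outside 3–180 s in the percentile interval as '<3 s' or '>180 s', neither dropped nor extrapolated. State in advance that EC80 may be reported as a lower bound only (not reached within 180 s).
3. Beside EC80, report the planned non-parametric profile, fitted as monotone, as the arrest rate at each of the nine times and its difference from the 180-s arm, with cluster-bootstrap 95% intervals. These exist whether or not 80% is reached.

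The cost is wording and analysis code, settled before outcome data are analysed; no children or visits are added. The downside is that EC80 may be published without an upper limit.
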